## Abstract

**Background:**

An inappropriate anastomosis method during laparoscopic anterior rectal resection can increase the risk of anastomotic complications and affect surgical, economic, and oncological outcomes. The aim of this study is to compare the incidence of anastomotic complications and the surgical, economic, and oncological outcomes following single versus double purse-string anastomosis during laparoscopic total mesorectal excision (TME) for low rectal cancer.

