**Methods/design:**

This randomized controlled trial (the SINGLE–DOUBLE study) will randomly assign middle and low rectal adenocarcinoma patients to receive either single or double purse-string anastomosis during laparoscopic low anterior rectal resection. Patients will be eligible for inclusion only if they (1) have adenocarcinoma confirmed by preoperative colonoscopy and biopsy, (2) have a tumor situated less than 12 cm from the anal verge, (3) do not have the anal sphincter involved, and (4) do not have distant metastases. The primary endpoint measure will be the incidence of anastomotic complications (leakage, narrowing, and bleeding). The secondary endpoints will be surgical, economic, and oncological outcomes. A total of 500 patients will be enrolled in the study. Sample size calculation was based on previous reports and our retrospective analysis.

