**Discussion:**

This randomized single-center controlled trial is expected to demonstrate which anastomosis method (single or double purse-string anastomosis) is better for reducing complications and improving prognosis in rectal cancer patients undergoing laparoscopic TME for low or middle rectal cancer.

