In 1979, Ravitch and Steichen [14] first proposed the end-to-end anastomosis for low rectal cancer. This procedure was improved by the use of a straight-line stapler (TA-55) to close the distal rectal segment, an end-to-end colorectal anastomosis performed using double staplers, and a tubular stapler inserted through a linear stapler via the anus. According to Griffen et al. [15], this kind of anastomosis has several advantages: (1) it avoids the technical difficulties involved in distal rectal suturing, (2) it makes anus-preserving surgery in lower rectal cancer technically feasible, (3) it reduces the possibility of contamination because the distal rectal segment is not opened, and (4) it makes it possible to connect intestinal segments of different diameters (the wider rectal ampulla and the narrower sigmoid colon) and thus reduces the complications of anastomosis. This anastomosis method is now widely applied, and laparoscopic linear stapling is used to close rectal stump. However, with its increasing use, some disadvantages are becoming apparent. This kind of anastomosis is usually a combination of an end-to-end anastomosis and an end-to-side anastomosis, which results in an incomplete internal wall of the anastomosis and increased scope of anastomosis, thus increasing the risk of bleeding. In addition, there is often poor blood supply to the anastomotic triangle, which further increases the risk of anastomotic leakage. Generally, purse-string sutures are used to close the proximal and distal rectum end-to-end colorectal anastomosis by a single stapler can provide a smooth inner wall at the anastomosis and reduce the length of the anastomosis. Double purse-string anastomosis by a single stapler can provide a smooth inner wall at the anastomosis and reduce the length of the anastomosis. However, the procedure is difficult to perform within the confines of the pelvic space.

This randomized controlled trial aims to determine whether there is a difference in the incidence of anastomotic complications (leakage, narrowing, and bleeding) and various surgical, economic, and oncological outcomes between patients receiving single purse-string anastomosis versus double purse-string anastomosis during laparoscopic TME for low rectal adenocarcinoma.

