### Study population

The study population will comprise patients with rectal cancer. The inclusion criteria will be (1) low or middle rectal adenocarcinoma, in which the tumor is situated less than 12 cm from the anal verge, (2) diagnosis confirmed by preoperative colonoscopy and biopsy, (3) patient eligible for low anterior rectal resection with laparoscopic TME, and (4) willingness for complete 5-year clinicopathological follow-up. Exclusion criteria will be (1) low rectal adenocarcinoma with anal sphincter involvement, (2) presence of distant metastases, (3) radical resection not performed because of local invasion, (4) presence of other synchronous malignancy or serious disease, and (5) surgery performed as an emergency procedure.

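### The aim is worded for low rectal cancer, but the trial enrols and will conclude on low and middle tumors, so the pooled result does not by itself answer the stated aim

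*Protocol article*

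**What the plan says.** All references are to the protocol article.

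- **Aim.** The Abstract's Background sets the comparison as "single versus double purse-string anastomosis during laparoscopic total mesorectal excision (TME) for low rectal cancer". The closing paragraph of the main Background repeats the restriction: "during laparoscopic TME for low rectal adenocarcinoma".
- **Who is enrolled.** The Abstract's Methods/design says that the trial "will randomly assign middle and low rectal adenocarcinoma patients". The first inclusion criterion under Study population is "low or middle rectal adenocarcinoma, in which the tumor is situated less than 12 cm from the anal verge".
- **Intended conclusion.** The Abstract's Discussion looks for the better method in "rectal cancer patients undergoing laparoscopic TME for low or middle rectal cancer".
- **Allocation and analysis.** Randomization and blinding gives 1:1 allocation and names no stratification factor. Statistical analysis mentions no analysis by tumor height. Preoperative evaluation does record each tumor's distance from the anal margin.
- **Sample size.** Power calculation and sample size uses one pair of leakage rates for laparoscopic low anterior resection (8.3% and 1.8%), not separated by height.

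**The concern.** The aim names one population, while eligibility and the intended conclusion name a larger one that contains it. A trial that meets its enrolment target will produce a single effect estimate averaged over low and middle tumors. If that estimate is reported against the aim as written, a statement about low rectal cancer would rest partly on patients who did not have it.

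The share of low tumors matters in two ways. It decides how far the pooled estimate reflects low tumors, and it decides how many patients bear directly on the stated aim. The article fixes no minimum for that share, and the 500 patients were sized for the whole group.

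**Working it through.** **1. Do the population statements agree?**

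| Place | Population |
|---|---|
| Abstract, Background (aim) | low |
| Background, last paragraph (aim) | low |
| Abstract, Methods/design | middle and low |
| Study population, criterion 1 | low or middle, under 12 cm |
| Abstract, Discussion (conclusion) | low or middle |

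The two statements of aim agree with each other, and so do the other three, but the two sets differ. Condensing a longer protocol does not explain this, because the article prints both versions.

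**2. Reproduce the plan's sample size.** Inputs from Power calculation and sample size: p1 = 0.083, p2 = 0.018, α = 0.05 (taken as two-sided), power 0.80.

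Variance term: V = p1(1 − p1) + p2(1 − p2) = 0.076111 + 0.017676 = 0.093787.

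n per arm = V × (1.960 + 0.842)² / (0.065)² = 174.2, which is the stated 174. With 20% dropout, 174 / 0.8 = 217.5, so 218 per arm and 436 in total, as stated. The arithmetic is sound.

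**3. Power for the whole sample.** 250 per arm less 20% leaves 200 evaluable per arm. Power = Φ(0.065 / √(V/n) − 1.960). At n = 200 this is Φ(3.002 − 1.960) = 85%.

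**4. Power for leakage in low tumors alone.** The low-tumor share f is not in the article and is assumed here. The plan's rates are applied unchanged to low tumors, which is a second assumption.

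| Assumed f | Evaluable per arm (200 × f) | 0.065 / √(V/n) | Power |
|---|---|---|---|
| 40% | 80 | 1.898 | 48% |
| 50% | 100 | 2.122 | 56% |
| 60% | 120 | 2.325 | 64% |
| 100% | 200 | 3.002 | 85% |

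A pooled-variance version gives 47%, 56% and 63% for the first three rows. Reaching the plan's 174 per arm among low tumors would need f of at least 174 / 200 = 87%.

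**5. Expected leaks in low tumors.** At f = 40 to 60%, 80 to 120 patients per arm give about 6.6 to 10.0 leaks in the single purse-string arm (80 × 0.083; 120 × 0.083) and 1.4 to 2.2 in the double purse-string arm (80 × 0.018; 120 × 0.018). An estimate from so few events will be imprecise.

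**6. Chance imbalance without stratification.** With f = 50% and 250 per arm, the difference between arms in the low-tumor share has a 95% range of ±1.96 × √(2 × 0.5 × 0.5 / 250) = ±8.8 percentage points. Adjusting for height in the analysis deals with this.

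**The case against.** The strongest reply is that the operative population is clear. Eligibility, the Abstract's Methods/design and the intended conclusion all say low or middle, and the sample size is for low anterior resection in general. On that view only the aim is loosely worded, and low power in a subgroup is ordinary. Much of this stands: the trial can answer a question about middle and low tumors, and it is sized for one. What remains is that the aim, stated twice, is a different question.

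A reader might infer more than the article supports:

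- *That the mix will be unknown.* It is unknown only at the design stage, because tumor distance is recorded at baseline.
- *That the comparison is biased.* Randomization protects the pooled comparison, and a comparison within a baseline height group is also unbiased, only less precise.
- *That allocation is unstratified.* The article gives the ratio and the software and says nothing further. A condensed article may leave stratification factors to the full protocol, so this silence is not an error.
- *That by the article's own reasoning the techniques differ between low and middle tumors.* The Background and Discussion say that the narrow pelvis makes both the distal purse-string and the linear stapler difficult. Neither compares low with middle tumors. The Background's remark that controversy is greatest in low rectal cancer concerns the debate, not a difference in effect.

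The power figures also have limits. They rest on an assumed share, they carry over rates that are not specific to low tumors, and they concern leakage alone, whereas the primary endpoint also includes narrowing and bleeding.

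**Conclusion.** The point holds as a mismatch of target population. The aim is confined to low rectal cancer, while enrolment and the expected conclusion cover low and middle tumors under 12 cm. The pooled result therefore does not by itself answer the aim as written.

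For scale, if 40 to 60% of patients have low tumors and the plan's leakage rates and 20% dropout apply to them, power for leakage in low tumors is about 48 to 64%, against about 85% for the whole sample. This illustrates how little the trial may say about low tumors separately. It is not an error in the sample size, which reproduces, and it is not power for the composite primary endpoint.

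The mismatch should be corrected, because it decides which patients the headline result may be applied to.

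**What to change.** 1. In the Abstract's Background and the last paragraph of the Background, state the objective for middle and low rectal adenocarcinoma, to match eligibility and the intended conclusion.
2. Prespecify the treatment effect on anastomotic complications, with its confidence interval, for low and for middle tumors, using the recorded distance from the anal margin. Fix the dividing height in advance.
3. Adjust the primary comparison for tumor height. A logistic model for anastomotic complications is already planned, so this adds one term.
4. Confine any statement on low rectal cancer to the low-tumor estimate.
5. If recruitment has not begun, also stratify the randomization by tumor height. The article is inconsistent here: Trial status says that recruitment is not yet open, while Study design says that the trial began in September 2018. If patients have already been allocated, items 1 to 4 still apply and the adjustment in item 3 takes on this role.

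The cost is a change of wording, one model term, one table and, where still possible, one stratification factor. The price is that the low-tumor estimate will be imprecise and the headline claim broader and less specific than the present aim.

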**Methods/design:**

This randomized controlled trial (the SINGLE–DOUBLE study) will randomly assign middle and low rectal adenocarcinoma patients to receive either single or double purse-string anastomosis during laparoscopic low anterior rectal resection. Patients will be eligible for inclusion only if they (1) have adenocarcinoma confirmed by preoperative colonoscopy and biopsy, (2) have a tumor situated less than 12 cm from the anal verge, (3) do not have the anal sphincter involved, and (4) do not have distant metastases. The primary endpoint measure will be the incidence of anastomotic complications (leakage, narrowing, and bleeding). The secondary endpoints will be surgical, economic, and oncological outcomes. A total of 500 patients will be enrolled in the study. Sample size calculation was based on previous reports and our retrospective analysis.

**Discussion:**

This randomized single-center controlled trial is expected to demonstrate which anastomosis method (single or double purse-string anastomosis) is better for reducing complications and improving prognosis in rectal cancer patients undergoing laparoscopic TME for low or middle rectal cancer.

**Trial registration:**

Registration number: ChiCTR1800016116. Protocol Registration Receipt: May 13, 2018.

**Electronic supplementary material:**

The online version of this article (10.1186/s13063-019-3411-7) contains supplementary material, which is available to authorized users.

## Background

Colorectal cancer is the third most common malignancy in both sexes worldwide [1]. Almost one third of colorectal cancers are located in the rectum and these are reported to be associated with worse prognosis [2–4]. Total mesorectal excision (TME) has been the gold standard treatment for locally advanced rectal cancer ever since Heald et al. first described it in 1982 [5]. With TME, it is possible to radically excise the cancer with relatively little damage to surrounding tissues. It maximizes functional outcomes, greatly reduces the risk of local recurrence, and promotes survival [6].

With the rapid advances in laparoscopic technology over the past 20 years, the advantages of laparoscopic surgery have become more and more obvious: it provides better cosmetic outcome, causes less tissue trauma and postoperative pain, and decreases the risks of wound infection, postoperative respiratory complications, and incisional hernia [7]. Therefore, laparoscopic TME has replaced open TME as the gold standard for rectal cancer surgery [8–10]. However, some controversies persist about which type of anastomosis is best for reducing the incidence of anastomotic complications [11–13], especially during laparoscopic TME for low rectal cancer.

In 1979, Ravitch and Steichen [14] first proposed the end-to-end anastomosis for low rectal cancer. This procedure was improved by the use of a straight-line stapler (TA-55) to close the distal rectal segment, an end-to-end colorectal anastomosis performed using double staplers, and a tubular stapler inserted through a linear stapler via the anus. According to Griffen et al. [15], this kind of anastomosis has several advantages: (1) it avoids the technical difficulties involved in distal rectal suturing, (2) it makes anus-preserving surgery in lower rectal cancer technically feasible, (3) it reduces the possibility of contamination because the distal rectal segment is not opened, and (4) it makes it possible to connect intestinal segments of different diameters (the wider rectal ampulla and the narrower sigmoid colon) and thus reduces the complications of anastomosis. This anastomosis method is now widely applied, and laparoscopic linear stapling is used to close rectal stump. However, with its increasing use, some disadvantages are becoming apparent. This kind of anastomosis is usually a combination of an end-to-end anastomosis and an end-to-side anastomosis, which results in an incomplete internal wall of the anastomosis and increased scope of anastomosis, thus increasing the risk of bleeding. In addition, there is often poor blood supply to the anastomotic triangle, which further increases the risk of anastomotic leakage. Generally, purse-string sutures are used to close the proximal and distal rectum end-to-end colorectal anastomosis by a single stapler can provide a smooth inner wall at the anastomosis and reduce the length of the anastomosis. Double purse-string anastomosis by a single stapler can provide a smooth inner wall at the anastomosis and reduce the length of the anastomosis. However, the procedure is difficult to perform within the confines of the pelvic space.

This randomized controlled trial aims to determine whether there is a difference in the incidence of anastomotic complications (leakage, narrowing, and bleeding) and various surgical, economic, and oncological outcomes between patients receiving single purse-string anastomosis versus double purse-string anastomosis during laparoscopic TME for low rectal adenocarcinoma.

## Methods/design

### Study design

This prospective single-center randomized clinical trial to be conducted at the Taizhou People’s Hospital of Jiangsu Province began in September 2018 and is expected to end in 2023. Patients with diagnosed rectal cancer and meeting the entry criteria will be recruited and randomly assigned to receive either single purse-string anastomosis or double purse-string anastomosis. All operations will be performed by the same group of surgeons. Baseline demographic and clinical features, surgical indices, pathological findings, health economic indices, postoperative complications, local recurrence, distant metastasis, disease-free survival, and overall survival will be compared between the two groups. Figure 1 shows the schedule of enrollment and interventions, and assessment is provided in the Standard Protocol Items: Recommendations for Interventional Trials (SPIRIT). Figure 2 shows the study flow. The SPIRIT checklist is presented in Additional file 1.

**Fig. 1 Fig1:**
[figure not shown]
SPIRIT (Standard Protocol Items: Recommendations for Interventional Trials) diagram for schedule of enrollment, interventions, and assessments. Safety assessment includes routine blood, routine stool, routine urine, liver function, renal function, coagulation test, syphilis, hepatitis B virus (HBV), hepatitis C virus (HCV), HIV, and electrocardiogram. *Abbreviations*: *t1* 1 day after allocation, *t2* 1 day after surgery, *t3* 1 week after surgery, *t4* discharge from hospital, *t5* 1 month after surgery, *t6* 6 month after surgery, *t7* 1 year after surgery, *t8* 1 and a half years after surgery, *t9* 2 years after surgery, *t10* 3 years after surgery, *t11* 4 years after surgery, *t12* 5 years after surgery

**Fig. 2 Fig2:**
[figure not shown]
Study flowchart. TME: Total mesorectal excision

### Study population

The study population will comprise patients with rectal cancer. The inclusion criteria will be (1) low or middle rectal adenocarcinoma, in which the tumor is situated less than 12 cm from the anal verge, (2) diagnosis confirmed by preoperative colonoscopy and biopsy, (3) patient eligible for low anterior rectal resection with laparoscopic TME, and (4) willingness for complete 5-year clinicopathological follow-up. Exclusion criteria will be (1) low rectal adenocarcinoma with anal sphincter involvement, (2) presence of distant metastases, (3) radical resection not performed because of local invasion, (4) presence of other synchronous malignancy or serious disease, and (5) surgery performed as an emergency procedure.

### Primary and secondary endpoints

The primary endpoint will be the incidence of anastomotic complications (i.e., anastomotic leakage, anastomotic narrowing, and anastomotic bleeding). Anastomotic leakage will include clinical and subclinical anastomotic leakage. The diagnosis of clinical anastomotic leakage is based on the clinical manifestations and the extravasation of contrast medium after rectal enema showed on the computed tomography (CT) scan. However, the subclinical anastomotic leakage has only extravasation of contrast medium [16]. Anastomotic narrowing will include both clinically evident narrowing and subclinical narrowing proved by endoscopic examination at 6 months after surgery. On endoscopy, anastomotic stricture will be diagnosed when the diameter of the anastomotic stoma is less than 11 mm [17]. Anastomotic bleeding will be determined as early postoperative anastomotic bleeding or delayed bleeding, and the bleeding of rectum within the first four weeks after rectal anastomosis will be considered as the early postoperative anastomotic bleeding [18].

The secondary endpoints will be the surgical, economic, and oncological outcomes. Indices of surgical outcome will include surgery duration, intraoperative blood loss, anus retention ratio, ileostomy rate, the number of patients with changed method of anastomosis, bowel function recovery time, mean size of tumor, proximal margin status, distal margin status, number of lymph nodes harvested, and postoperative defecation and genitourinary dysfunction. Economic evaluation includes direct and indirect costs, direct costs will include duration of hospital stay and medical costs, and subsequent direct cost-effectiveness analysis will be performed. Indices of oncological outcome will include tumor-node-metastasis (TNM) stage, histology stage, local recurrence, distance metastasis, disease-free survival, and overall survival.

### Randomization and blinding

Patients meeting the eligibility criteria will be randomly assigned (1:1) to receive either single purse-string anastomosis or double purse-string anastomosis. Randomization will be performed by using TenAlea software (ALEA Clinical, Abcoude, The Netherlands).

Given the obviously different characteristics of the two types of anastomoses, blinding of the surgeons will not be possible. However, patients, nursing staff, and statisticians will be blinded to treatment allocation during data collection and analysis.

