### Data collection and monitoring

Patients will fill out questionnaires both before and after surgery. The operation will be performed by the same surgical team, and colonoscopies will be performed by the same senior endoscopic examiner. The study coordinators will be regularly contacted through monthly meetings. Two research fellows will enter the data into a Microsoft Access database every day.

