Surgical, economic, and oncological outcomes are also important indices of the feasibility and success of an operation. This study seeks to establish whether double purse-string anastomosis has any significant impact on surgical, economic, and oncological outcomes in patients undergoing low anterior rectal resection. Increase in the rate of anal preservation and reduction of defecation and genitourinary dysfunction following laparoscopic low anterior rectal resection will be an indication that the technique could improve the quality of life of patients [30]. Pre- and post-operative assessments of defecation and genitourinary function will allow complete evaluation of the impact of the operation. This randomized controlled trial will also avoid the biases inherent in retrospective evaluations. We expect that the double purse-string group will present fewer anastomotic complications, shorter hospital stays, and reduced medical costs.

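### The list of blinded roles leaves out whoever reads the endoscopies and CT scans and whoever judges bleeding, and no masked reading of the primary endpoint is provided for

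*Protocol article*

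**What the plan says.** The section on randomization and blinding has two parts. Because the two anastomoses look different, "blinding of the surgeons will not be possible". It then names three blinded groups: "patients, nursing staff, and statisticians will be blinded to treatment allocation during data collection and analysis".

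The section on primary and secondary endpoints defines the endpoint: "The primary endpoint will be the incidence of anastomotic complications (i.e., anastomotic leakage, anastomotic narrowing, and anastomotic bleeding". Its components are decided as follows.

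- **Leakage.** Clinical leakage needs clinical signs together with "extravasation of contrast medium after rectal enema showed on the computed tomography (CT) scan". Subclinical leakage rests on contrast extravasation alone.
- **Narrowing.** It covers clinically evident narrowing and subclinical narrowing found at endoscopy at 6 months. On endoscopy, "anastomotic stricture will be diagnosed when the diameter of the anastomotic stoma is less than 11 mm". The article does not say how the diameter is measured.
- **Bleeding.** It is classed as early (within four weeks) or delayed. No assessor is named.

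The section on postoperative evaluation adds colonoscopies at 1 and 3 months that look for leakage and stricture. The section on data collection and monitoring says that "colonoscopies will be performed by the same senior endoscopic examiner". The Discussion records the team's expectation: "We expect that the double purse-string group will present fewer anastomotic complications".

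**The concern.** When the operator cannot be blinded, masking the people who determine the outcome is the main protection against detection bias. Here the blinding section gives an explicit list of roles, and nobody on it is assigned the endoscopic or CT reading that decides narrowing and leakage. A diameter near 11 mm, or a doubtful track of contrast, is a call that knowledge of the technique could tip. One endoscopist performs all the colonoscopies, so any leaning of that person enters every borderline reading in the same direction and does not average out across readers. Bleeding has no named assessor, so the gap extends to all three components.

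At stake is whether a difference in the primary endpoint can be credited to the technique. If only a yes/no call is kept, by a reader who knew the arm, no analysis can undo the bias afterwards.

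**Working it through.** **1. Who is blinded, set against who decides.**

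| Component | Decided by | Stated as blinded? |
|---|---|---|
| Narrowing | endoscopy, one senior examiner, 11 mm cut-off | not stated |
| Leakage | contrast extravasation on CT, with or without clinical signs; colonoscopy also looks for it | not stated |
| Bleeding | no assessor named | not stated |

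No section shown provides for masked endoscopy, masked CT reading or masked adjudication.

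**2. The plan's own figures.** These fix the number of evaluable patients used below. The power calculation gives leakage of 8.3% and 1.8%, α = 0.05 (two-sided assumed), power 0.80 and 20% dropout.

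- n per group = [p1(1−p1) + p2(1−p2)] × (1.960 + 0.842)² / (p1−p2)² = (0.0761 + 0.0177) × 7.849 / 0.004225 = 174.2. The article states 174, so its figure is reproduced.
- 174 / 0.80 = 217.5, so 218 per group and 436 in total, as stated.
- Planned enrolment is 250 per group; 250 × 0.80 = 200 evaluable per group.

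Assessor blinding enters none of these figures.

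**3. Illustration for narrowing alone.** Assumptions: no true difference; narrowing 20% in both arms (the Discussion reports stricture rates up to 20%, so this is an upper figure); 200 evaluable per arm; a differential reading of d points between arms. The documents give no value for d, so a range is shown.

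- SE of the difference = √(2 × 0.20 × 0.80 / 200) = 0.040.
- False-positive rate = P(Z > 1.96 − d/SE) + P(Z < −1.96 − d/SE).

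| d (points) | d/SE | Upper + lower tail | Two-sided false-positive rate |
|---|---|---|---|
| 0 | 0 | 0.025 + 0.025 | 5% |
| 1 | 0.25 | 0.0436 + 0.0136 | 5.7%, about 6% |
| 2 | 0.50 | 0.0721 + 0.0069 | 7.9%, about 8% |
| 3 | 0.75 | 0.1131 + 0.0034 | 11.7%, about 12% |

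**4. Sensitivity, with under-calling as a proportion.** Suppose events are under-called by a fixed fraction in the double purse-string arm only. The chance of a false significant result favouring that arm (nominally 2.5%) is Φ[(difference − 1.96 × pooled SE) / unpooled SE], with 200 per arm.

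| True rate, both arms | 10% under-called | 20% | 30% | 50% |
|---|---|---|---|---|
| Narrowing 20% | 7% | 18% | 36% | 80% |
| Narrowing 10% (assumed) | 5% | 10% | 19% | 48% |
| Leakage 8.3% (the single purse-string figure, assumed for both arms) | – | 9% | – | 40% |

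The inflation depends heavily on the base rate and on the size of the reading difference, neither of which the documents fix.

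**The case against.** **The text is silent.** A reader might infer that the endoscopist and a radiologist are unblinded. The article does not say so. It rules out blinding only for surgeons, and it mentions no radiologist; a CT reader is inferred from the leakage criterion. This objection stands, and the point is limited to what is not listed and not provided for.

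**This is a condensed article.** The SPIRIT checklist is in an additional file that is not shown, and reading procedures may be set out in a fuller protocol. This stands in part. But the article does more than omit a detail: it gives a list of blinded roles and leaves out an endoscopist whom it identifies elsewhere. If assessors are in fact masked, the list is incomplete and should say so.

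**Safeguards exist.** There is a numeric threshold, an imaging criterion for leakage, the same planned examinations with no difference stated between arms, blinded patients and a single endoscopist. These limit differential symptom reporting, unequal scheduling and between-reader noise. They do not prevent a reader who knows the arm from leaning on borderline calls.

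**The technique may be visible anyway.** The section on blinding begins "Given the obviously different characteristics of the two types of anastomoses", and the Background and Discussion describe a smooth inner wall against residual corners. This stands for endoscopy. Having a blinded statistician apply the 11 mm rule would remove no bias if the measurement came from someone who had recognised the technique. It has much less force for CT reading.

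**Two further inferences are not supported.** No rate is given for subclinical narrowing, so it cannot be called the most frequent component. Nor does the article present the blinding of nursing staff as a substitute for blinding assessors.

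**Conclusion.** The point holds as a gap in the stated blinding: three roles are listed, the assessors of all three components of the primary endpoint are not among them, and no masked reading or adjudication is provided for. Followed as written, the plan leaves the primary endpoint open to detection bias, and the article states an expectation in favour of one arm.

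For narrowing alone, at 20% in both arms and 200 evaluable per arm, the two-sided false-positive rate goes from 5% to about 6%, 8% or 12% for a differential of 1, 2 or 3 points. This shows how sensitive the test is. It is not an estimate of bias: the differential is assumed, the 20% is an upper figure, and one component is tested rather than the composite. Nothing in the documents shows that biased reading has occurred or will occur. The change should be made, but it does not call the sample size or the randomization into question.

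**What to change.** In the section on randomization and blinding, add to the blinded roles the CT reader, the endoscopist, and whoever classifies bleeding and leakage events. If these people are already masked under a fuller protocol, say so there.

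To put it into practice:

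- Send endoscopy and CT requests under the study number only, with the operative note withheld.
- Have the anastomotic diameter measured by one standard, stated method and recorded in mm before the 11 mm rule is applied.

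The cost is request-form wording and one extra recorded value, with the same staff and the same examinations. The downside is that the staple line may reveal the technique at endoscopy, so masking there is partial and should be reported as a limitation. CT reading can be masked more fully.
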